### Sample size calculation

A sample size of 104 subjects was estimated for 80% power at a significance level of 0.05 and an attrition rate of 20%. Participants will be selected according to the eligibility criteria.

No preliminary studies of TJ001 were available to aid in estimating the percentage of subjects with 5% or greater weight loss [21]. Therefore, we set the rate at 40% for the TJ001 group and 13% for the placebo group on the basis of a reference paper [28]. The formula for calculating the sample size when allocating subjects at a ratio of 1:1 (TJ001:placebo) is as follows:

$$\begin{array}{c} n=\frac{{\left\{z_{1-\alpha }\sqrt{2\bar{p}\left(1-\bar{p}\right)}+z_{1-\beta }\sqrt{p_{t}\left(1-p_{t}\right)+p_{c}\left(1-p_{c}\right)}\right\}}^{2}}{{\left(p_{t}-p_{c}\right)}^{2}}\\ \;=\frac{{\left\{1.96\sqrt{2\left(0.265\right)\left(0.735\right)}+0.84\sqrt{\left(0.40\right)\left(0.735\right)+\left(0.13\right)\left(0.87\right)}\right\}}^{2}}{{\left(0.40-0.13\right)}^{2}}\approx 41 \end{array}$$

p_t_

The 5% or greater responder rate of the initial weight in TJ001 group = 40%.

p_c_

The 5% or greater responder rate of the initial weight in the placebo group = 13%.

$$\bar{p}:\left(p_{t}+p_{c}\right)/2=26.5\%\;z_{1-\alpha /2}=1.96,\;z_{1-\beta }=0.84$$

Allowing for an attrition rate of 20%, the number of subjects in each group is 52.

$$n^{*}=\frac{n}{\left(1-0.2\right)}=51.25\approx 52$$

Therefore, a total of 104 subjects are needed for this trial.

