### Randomisation method

The study subjects who satisfy the eligibility criteria will be randomised using a web-based randomisation program at an independent centre (Medical Research Collaborating Center of Seoul National University Hospital http://mrcc.snuh.org/). This program will be set to allocate participants equally to each site at a ratio of 1:1. Each of the four sites will be allocated 26 participants. The TJ001 and placebo groups will each be allocated 52 participants. The randomisation program will be designed with a four-patient block randomisation.

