#### Secondary outcomes

Both within-group and between-group analyses will be performed for each outcome. The differences in the following variables between the baseline (visit 1) and the last visit (visit 5) will be calculated.

• Body weight (kg)

• BMI (kg/m^2^)

• WC (cm)

• HC (cm)

• Waist/hip circumference ratio (WHR) change

Lipid profile: total cholesterol, triglyceride, HDL cholesterol, LDL cholesterol levels (mg/dl) (LDL cholesterol will be estimated using the Friedewald equation [33].)

Body fat composition: visceral fat area (cm^2^) and subcutaneous fat area (cm^2^) (Body composition will be evaluated by abdominal computed tomography.)

• Blood pressure (mmHg)

• Fasting plasma glucose concentration (mg/dl)

• C-reactive protein (mg/L) Questionnaires scores: Korean Obesity-related Quality of Life (KOQOL) and Korean version of Eating Attitudes Test-26 (KEAT-26)

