### Statistical analysis

#### Efficacy assessment

The primary outcome will be analysed using the intention-to-treat (ITT) method. The secondary outcomes will be assessed by both the ITT and the per-protocol (PP) methods. The full analysis set for ITT method will include all randomised subjects, regardless of their subsequent withdrawal after enrolment. The PP analysis will include patients who have completed the 12-week study term without any major protocol violations and have a compliance rate > 70%. Missing values will be replaced by using the last observation carried forward method. Continuous variables will be reported as means ± SD, and categorical variables will be reported as percentages. The baseline characteristics will be compared by either Student's *t*-test for continuous variables or the χ^2 ^test (Fisher's exact test when the expected value is < 5) for categorical data. Alternatively, McNemar's test will be used if the normality assumption is not satisfied for the continuous variables.

For the within-group analyses, primary and secondary outcome variables will be evaluated by using a paired *t*-test. Alternatively, for nonnormal distribution data, the Wilcoxon test will be performed. Analysis of covariance will be applied to analyse differences in each group at every visit, adjusting for age, baseline weight and BMI as covariates. Between-group comparisons for each variable will be performed using Student's *t*-test. Statistical significance will be defined as *P *< 0.05. PASW for Windows version 18.0 software (SPSS, Inc, Chicago, IL, USA) will be used for the analyses.

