## Discussion

By exploring estimated obesity-related variables, our aim in this pilot study is to determine the precise target population, the primary end point and the intervention period. Throughout the trial we will evaluate the efficacy and safety of Taeumjowi-tang. Korea has a dual medical treatment system, and herbal medicine assessments are under special regulations as described in the WHO legal status review of traditional medicine. For traditional Korean medicinal herbs, the Korea Food and Drug Administration rules specify that they are permitted to be produced [34,35] if herbal preparations are listed in the 11 classic traditional Korean and Chinese medicine books [36]. As these preparations are considered to have historical evidence of efficacy and safety, clinical or toxicological results can be exempted. Our intervention, Taeumjowi-tang, is described in one of these classic medical books, the *Donguisusebowon *[8]. Despite its long history and widespread usage, few Taeumjowi-tang trials have been published [21,27,37]. Therefore, our trial could be considered a pilot study, and the efficacy and safety of Taeumjowi-tang should be assessed in a RCT.

We encountered difficulties in deciding several issues. First, we had difficulty in selecting the target population. We considered using stratified randomisation, because weight reduction is affected by sex, age and physical baseline characteristics such as initial weight and BMI [3,38,39]. However, these various strata would decrease the statistical power. We first needed to determine the general patterns of Korean obesity. To maximise both the power and the results within given research budgets, we will include adults over age 18 years and both sexes. We will carry out stratified analyses with sex as a stratum. Other covariates, such as age, weight and BMI at the initial screening visit, will be adjusted.

The second question was what the primary end point would be. Among various outcomes [40,41], we set a 5% or greater weight loss responder rate as the primary outcome because 5% or greater weight loss is considered to be clinically significant [28,30,32]. As the amount of weight loss can vary due to initial weight, our study team concluded that the rate of the subjects who achieved a weight loss of 5% or more from their baseline weight would be reasonable compared to the absolute weight change. Other parameters, such as BMI, weight, body fat composition and WHR, were set as secondary outcomes.

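### For the continuous secondary outcomes the protocol plans an adjusted ANCOVA and an unadjusted t-test without saying which decides; most outcomes lack their own baseline as covariate, and site is in no analysis

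*Protocol article*

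**What the plan says.** Four places in the protocol article bear on this.

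- **Efficacy assessment.** Within-group change is tested by paired t-test or Wilcoxon test. An ANCOVA follows, worded as examining differences in each group visit by visit, "adjusting for age, baseline weight and BMI as covariates". The next sentence reads "Between-group comparisons for each variable will be performed using Student's" *t*-test. One threshold, P < 0.05, covers everything, and no order of precedence is given.
- **Secondary outcomes.** "Both within-group and between-group analyses will be performed for each outcome". The outcomes are defined as change from baseline to visit 5.
- **Randomisation method.** "This program will be set to allocate participants equally to each site at a ratio of 1:1", with 26 subjects at each of four sites, 52 per arm, and blocks of four.
- **Discussion.** "We will carry out stratified analyses with sex as a stratum". Age, weight and BMI are again named as adjustment variables. Stratified randomisation on patient factors was considered and not used; site is not discussed there.

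**The concern.** Two analyses are named for the same continuous outcomes, and the text leaves their roles open. If the ANCOVA is meant as a treatment comparison, each outcome has two P values and no rule for choosing between them. If its wording about differences in each group is taken literally, the only treatment comparison is the unadjusted t-test, and the adjustment promised in the Discussion never reaches it. Either way the analyst must decide something that the protocol should have settled.

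One covariate set serves every outcome. For waist circumference, lipids, CT fat areas, blood pressure, glucose, CRP and the questionnaires, the strongest available predictor of the week-12 value is probably the same measure at baseline, and it is not in the model. Site, which appears to have governed allocation, is also left out. One stated objective is to estimate obesity-related variables for a larger trial, so precise and unambiguous estimates are a main product of this pilot.

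Within-group tests add a third set of P values. All participants agree to a low-calorie diet, so a fall in weight is to be expected on placebo too.

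**Working it through.** **1. The plan's own figure.** Inputs from the Sample size calculation section: "we set the rate at 40% for the TJ001 group and 13% for the placebo group", two-sided 0.05 (1.96), 80% power (0.84), 20% attrition.

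n = {1.96·√(2·0.265·0.735) + 0.84·√(0.40·0.60 + 0.13·0.87)}² / 0.27² = 40.70, so 41 per arm. Then 41/0.8 = 51.25, so 52 per arm and 104 in total. This agrees with the article. It rests on an unadjusted comparison of two proportions, so nothing below changes it.

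**2. Which outcomes lack their own baseline.** Counting blood pressure once: weight, BMI, WC, HC, WHR, four lipids, two CT fat areas, blood pressure, glucose, CRP, KOQOL, KEAT-26 = 16. Weight and BMI have their own baselines as covariates; 14 do not. Table 4 shows that each is measured, or can be derived, at visit 1 or visit 2.

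**3. Gain from the own baseline.** Let rho be the correlation between baseline and week 12, with equal variance σ² at both. The article gives no rho, so it is an assumption.

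- Variance of change: 2σ²(1 − rho)
- Residual variance after own-baseline ANCOVA: σ²(1 − rho²)
- Ratio: (1 − rho²) / {2(1 − rho)} = (1 + rho)/2

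| rho | variance ratio | CI width ratio (square root) | CI narrower by | power, if t-test has 80% |
|---|---|---|---|---|
| 0.5 | 0.75 | 0.866 | 13% | 90% |
| 0.7 | 0.85 | 0.922 | 8% | 86% |
| 0.8 | 0.90 | 0.949 | 5% | 84% |

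**4. Comparison with the planned ANCOVA, and the effect of site.** Simulation of 104 subjects: four sites of 26, permuted blocks of four within site, no dropout, 4,000 runs per setting. The true effect was set so that a t-test with 52 per arm has 80% power. Assumed: weight and BMI correlated 0.8, the outcome's baseline correlated 0.3 with weight, and a site intraclass correlation (ICC) of 0 or 0.10.

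| rho | ICC | t-test on change | planned ANCOVA | + own baseline | + own baseline and site |
|---|---|---|---|---|---|
| 0.5 | 0 | 79% | 79% | 88% | 88% |
| 0.5 | 0.10 | 77% | 77% | 85% | 88% |
| 0.8 | 0 | 79% | 78% | 81% | 81% |
| 0.8 | 0.10 | 77% | 77% | 80% | 83% |

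Under these assumptions the planned covariates gain nothing over the t-test. The own baseline accounts for most of the improvement, and site adds 0 to about 3 points. With no treatment effect and ICC 0.10, the t-test rejected in 4.3% to 4.4% of runs, which is slightly conservative.

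**5. Cost of having two P values.** Across the settings run (ICC 0, 0.05 and 0.10), the t-test and the planned ANCOVA disagreed on significance in about 1% to 2% of null trials and 5% to 6% of trials with a true effect. Taking the smaller P gave a type I error of about 5% to 6.4%.

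**6. Site and the responder comparison.** The comparison here is an unstratified chi-square against a site-stratified (CMH) test. The chi-square is itself an assumption, because the article assigns that test only to baseline characteristics. With a between-site SD of 0.6 on the logit scale, the chi-square has a type I error of about 4.5% to 4.8% and loses about 0.5 points of power. At SD 0.9 to 1.2, which is implausibly large, the figures are 3.6% to 4.2% and 1.4 to 2.3 points. If sites are alike, CMH loses under 0.5 points.

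**7. Within-group tests (illustration).** Assume a mean placebo loss of 1.3% with SD 3.3%. The share losing 5% or more is P(Z ≥ (5 − 1.3)/3.3 = 1.12), about 13%, which is the planned placebo rate. With 52 subjects the test statistic is centred at 1.3/(3.3/√52) = 2.84, so a paired test on placebo alone has about 80% power.

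**The case against.** The strongest reply is that a condensed article leaves covariates and precedence to the analysis plan, that these are secondary outcomes of a declared pilot, and that the effects are modest. The first part does not answer the point. The article does not leave the covariates open: it fixes one set for all outcomes and then names a different, unadjusted test in the next sentence. The second and third parts stand, and they limit the weight of the point.

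Several stronger readings are tempting, and the text does not support them.

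- *No outcome is adjusted for its own baseline.* Not so for body weight and BMI. For the rest, the t-test on change also uses baseline, by subtraction, though less efficiently.
- *The t-test is a fallback.* It is the test named for between-group comparisons. Two competing P values arise only if the ANCOVA is read as a treatment comparison.
- *The analysis ignores a declared stratification factor and so risks false positives.* Site is never called a stratum; that follows only by inference from the allocation description. Leaving it out makes the tests conservative.
- *The missing sex term contradicts the Discussion.* The Discussion promises separate analyses stratified by sex, not a covariate.
- *Weight and BMI should not both be adjusted for.* Including both costs one degree of freedom and does not bias the treatment effect. Dropping one is a preference.
- *Within-group significance is to be used as evidence for TJ001.* No section says so, and the stated hypothesis is a comparison with placebo.

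**Conclusion.** The point holds in limited form. For the continuous secondary outcomes, the article names an adjusted and an unadjusted analysis without precedence, fixes a covariate set that lacks the own baseline of 14 of about 16 variables, and includes site in neither analysis.

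The main loss is precision. Against the change-score t-test, intervals could be about 5% to 13% narrower for rho between 0.8 and 0.5, which assumes equal variances at baseline and week 12. The gain from site is small, and zero if sites are alike. The ambiguity over which P value decides costs little in type I error, but it leaves an avoidable choice open after the data are seen. The 104 subjects and the assumptions behind them are unaffected. This should be corrected, but it does not threaten the trial's main comparison.

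**What to change.** - For each continuous secondary outcome, name one decisive between-group analysis: ANCOVA of the week-12 value on treatment, that outcome's own baseline, site, and the planned covariates (age, baseline weight, BMI).
- State which visit supplies each baseline. The Secondary outcomes section gives visit 1, but in Table 4 lipids, CRP, CT and the two questionnaires are first measured at visit 2.
- Drop the Student's t-test, or label it supportive.
- Report within-group changes descriptively and not as evidence of efficacy.
- Stratify the primary responder comparison by site, for example with a CMH test.

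The change is one of wording, because every variable is already collected. It should be made before unblinding. The planned model uses 5 parameters (intercept, treatment, age, weight, BMI). Adding one own baseline and three site terms makes 9, so with 104 subjects the residual degrees of freedom fall from 99 to 95. If sites do not differ, the CMH test loses under 0.5 points of power. No extra subjects or visits are needed.

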#### Safety assessment

Safety analyses will be performed for all subjects, who will be randomised and visited more than once after the initial screening. Safety-related variables will be analysed using the ITT method. Safety data will be stratified according to symptoms.

### Adverse event reporting

AEs will be recorded in medical diagnostic terminology. Detailed symptoms, duration, severity, causal relationships, actions taken, results and other information will be recorded for each AE. All AEs must be observed and recorded in the CRF in the AE report section. When an AE occurs, investigators should notify both the IRB and the regulatory authorities within 24 hours.

### Data quality control, data collection and data management

Data quality control will be achieved through monitoring during the trial. After checking the written CRF, well-trained clinical research associates of the CRO will collect the data. Data management will be performed by the CRO, Center for Clinical Research and Genomics, Seoul, Republic of Korea. All processes will be conducted using standard operating procedures.

### Ethical issues

This study has been approved by the institutional review boards (IRBs) at each of the four institutions: the IRB of the Catholic University of Korea Seoul St Mary's Hospital (reference KC09MNME0032), the IRB of the Dongguk University Ilsan Oriental Hospital (ref: SR-09), the IRB of the Semyung University Oriental Medicine Hospital (reference 2008-03) and the IRB of the Kyungwon Gil Oriental Medical Hospital (reference 08-101)). Written informed consent will be obtained from each individual prior to enrolment. Research will be performed in compliance with the Helsinki Declaration and with the Good Clinical Practice Guidelines.

## Discussion

By exploring estimated obesity-related variables, our aim in this pilot study is to determine the precise target population, the primary end point and the intervention period. Throughout the trial we will evaluate the efficacy and safety of Taeumjowi-tang. Korea has a dual medical treatment system, and herbal medicine assessments are under special regulations as described in the WHO legal status review of traditional medicine. For traditional Korean medicinal herbs, the Korea Food and Drug Administration rules specify that they are permitted to be produced [34,35] if herbal preparations are listed in the 11 classic traditional Korean and Chinese medicine books [36]. As these preparations are considered to have historical evidence of efficacy and safety, clinical or toxicological results can be exempted. Our intervention, Taeumjowi-tang, is described in one of these classic medical books, the *Donguisusebowon *[8]. Despite its long history and widespread usage, few Taeumjowi-tang trials have been published [21,27,37]. Therefore, our trial could be considered a pilot study, and the efficacy and safety of Taeumjowi-tang should be assessed in a RCT.

We encountered difficulties in deciding several issues. First, we had difficulty in selecting the target population. We considered using stratified randomisation, because weight reduction is affected by sex, age and physical baseline characteristics such as initial weight and BMI [3,38,39]. However, these various strata would decrease the statistical power. We first needed to determine the general patterns of Korean obesity. To maximise both the power and the results within given research budgets, we will include adults over age 18 years and both sexes. We will carry out stratified analyses with sex as a stratum. Other covariates, such as age, weight and BMI at the initial screening visit, will be adjusted.

The second question was what the primary end point would be. Among various outcomes [40,41], we set a 5% or greater weight loss responder rate as the primary outcome because 5% or greater weight loss is considered to be clinically significant [28,30,32]. As the amount of weight loss can vary due to initial weight, our study team concluded that the rate of the subjects who achieved a weight loss of 5% or more from their baseline weight would be reasonable compared to the absolute weight change. Other parameters, such as BMI, weight, body fat composition and WHR, were set as secondary outcomes.

Third, we had difficulty in determining the treatment duration. Though a short-term medication period for chronic treatment may not be sufficient to observe accurate long-term effects [22,42], we prioritised feasibility. We decided on a 12-week treatment for the trial after reflecting on the opinions of the clinicians' general experiences and considering both the attrition rate and the effectiveness of the preparation. Attrition rate will increase if the treatment duration is prolonged for more than 3 months. Additionally, according to data reported in the literature [21,27,32,43,44], the intervention period of weight reduction ranges from 1 day to 18 months for complementary therapy RCTs. Among complementary therapy RCTs, 8-week and 12-week trials are the most common [23,26,27,44].

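### The Discussion promises analyses stratified by sex, but the Efficacy assessment section uses sex in no test or model

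*Protocol article*

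**What the plan says.** In the Discussion, the paragraph on choosing the target population says that weight reduction depends on sex, age and physical baseline characteristics. Stratified randomisation was considered for that reason and not adopted. The paragraph then states: "We will carry out stratified analyses with sex as a stratum". The next sentence reads: "Other covariates, such as age, weight and BMI at the initial screening visit, will be adjusted".

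The Efficacy assessment section takes up the second of these sentences but not the first. Its analysis of covariance is described as "adjusting for age, baseline weight and BMI as covariates". Between-group comparisons of each variable are by Student's t-test, with no adjustment. One rule covers everything: "Statistical significance will be defined as *P *< 0.05". Sex appears in none of these tests, models or covariate lists.

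The Sample size calculation section sizes the trial on the overall responder comparison alone: "we set the rate at 40% for the TJ001 group and 13% for the placebo group". The Randomisation method section fixes the arms: "The TJ001 and placebo groups will each be allocated 52 participants". It describes blocks of four and equal numbers per site, with no stratum for sex. Table 4 and its footnotes show that sex is recorded at visit 1.

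**The concern.** The factor that the Discussion singles out for stratification is the one that the analysis section leaves out. An analyst who follows the Efficacy assessment section would never run a sex-stratified comparison. One who follows the Discussion would run something that section does not describe.

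This matters in two ways. First, the authors regard sex as prognostic and did not balance it by design, so a comparison that ignores it gives up precision and leaves chance imbalance uncorrected. Second, the primary comparison can be produced with or without sex, and the article does not say which version decides.

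The wording also leaves room for a subgroup use of sex, because finding the precise target population is a stated objective. That use would have much larger statistical consequences, so it should be settled in the text.

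**Working it through.** **1. The two sections side by side**

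| Factor | Discussion | Efficacy assessment |
|---|---|---|
| Age | adjusted | ANCOVA covariate |
| Weight | adjusted | ANCOVA covariate |
| BMI | adjusted | ANCOVA covariate |
| Sex | stratum | not used |

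Three of the four factors match. Sex does not. If stratification means one pooled comparison stratified by sex, the analysis section plans no such test. If it means results within each sex, the analysis section does not plan those either. The mismatch stands on both readings.

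**2. The plan's own sample size**

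Inputs from the Sample size calculation section: rates 0.40 and 0.13, mean 0.265, z = 1.96 (two-sided) and 0.84.

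n = {1.96·√(2 × 0.265 × 0.735) + 0.84·√(0.40 × 0.60 + 0.13 × 0.87)}² / 0.27² = 40.7, so 41 per arm.

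41 / 0.8 = 51.25, so 52 per arm and 104 in total. The stated figures reproduce. (The printed line shows 0.735 where 1 − 0.40 = 0.60 belongs. Taken literally it gives 42.5, so the stated 41 comes from 0.60.) At 41 per arm, power is 80.3% for the overall comparison.

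**3. How far sex may be unbalanced by chance**

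Assume half the participants are women; the article gives no split. With 52 per arm, the standard deviation of the between-arm difference in the proportion of women is √(0.5 × 0.5 × 2/52) = 0.098, about 10 percentage points. The effect on the responder comparison cannot be computed, because no sex-specific responder rates are given. The unadjusted test keeps its 5% level. The loss is in precision.

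**4. Only if men and women were tested separately at 0.05, beside the overall test**

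*False positives.* Under no effect, the two sex-specific statistics Z₁ and Z₂ are independent, and the overall statistic is approximately √s·Z₁ + √(1−s)·Z₂, where s is one sex's share. The two sex tests alone give 1 − 0.95² = 9.75%. With the overall test added (2,000,000 simulated draws per row):

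| Sex split (assumed) | Any of three, two-sided | Any of three, favouring TJ001 |
|---|---|---|
| 50:50 | 11.5% | 5.8% |
| 70:30 | 11.3% | 5.7% |
| 80:20 | 11.2% | 5.7% |
| 90:10 | 10.8% | 5.5% |

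The reference values for one test are 5% and 2.5%. A single pooled test stratified by sex stays at those values.

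*Power within a sex.* At the planned rates, power = Φ[(0.27·√n − 1.96·√(2 × 0.265 × 0.735)) / √(0.40 × 0.60 + 0.13 × 0.87)], with n per arm within that sex:

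| Sex split (assumed) | 41 evaluable per arm | 52 per arm |
|---|---|---|
| 50:50 | 50% and 50% | 60% and 60% |
| 70:30 | 65% and 32% | 75% and 40% |
| 90:10 | 76% and 13% | 85% and 15% |

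At 50:50 with the same true effect in both sexes, significance in exactly one sex would occur in 2 × 0.50 × 0.50 = 50% of trials (41 evaluable), or 2 × 0.60 × 0.40 = 48% (52 analysed).

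**The case against.** The strongest reply is that the sections barely conflict. The Discussion handles sex by stratification and the other three factors by adjustment, so sex need not appear in the covariate list. The sentence follows the decision not to stratify randomisation and is followed by one about other covariates, which puts sex among the factors to be controlled. Read that way, it promises one pooled comparison stratified by sex, with no extra test and no loss of error control. The deciding comparison is also reasonably clear: one hypothesis, one primary outcome, analysis of all randomised subjects, and a sample size built on that comparison alone. The trial calls itself a pilot throughout.

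Much of this stands. A reader might infer that men and women will each be tested at 0.05 beside the overall test, so that the trial could be declared positive in one sex. The article does not say so, and the surrounding sentences fit the pooled reading at least as well. The subgroup reading is not excluded, given the target-population objective and the blanket significance rule, but it remains an inference. The lack of an interaction test or of an exploratory label for this analysis is not a fault in itself either, since an article may leave such detail to the full protocol or analysis plan.

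What the reply does not remove is the omission. On the pooled reading too, the Efficacy assessment section contains no stratified test. An unadjusted t-test and a covariance model without sex do not deliver what the Discussion promises.

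**Conclusion.** The point holds as an inconsistency between two sections of the same article. A collected factor that the authors call prognostic, and undertake to use as a stratum, is absent from every stated test and model. This does not invalidate the primary comparison. It costs some precision, in an amount the article's figures do not allow one to calculate, and it leaves open whether the deciding result is the one with or without sex.

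The figures of about 11% two-sided, 5.5% to 5.8% in favour of TJ001, and about 50% power per sex are conditional. They apply only if the sexes are tested separately at 0.05, and they rest on an assumed sex split. The 50% power figure also assumes 41 evaluable per arm and the planned rates in both sexes. They show why the wording should be settled and are not the operating characteristics of a stated plan.

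**What to change.** Make the Efficacy assessment section match the Discussion:

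- State that the deciding analysis is one pooled intention-to-treat comparison of responder rates with sex as a stratification factor, by a Mantel-Haenszel test or logistic regression including sex.
- Add sex to age, baseline weight and BMI in the analysis of covariance.
- If male and female results are also shown for the target-population objective, give estimates with 95% confidence intervals and a sex-by-treatment interaction, labelled exploratory, with no efficacy claim from one sex alone.

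This takes a few sentences. No new data are needed, because sex is recorded at visit 1, and the sample size is unchanged. The only thing given up is the option of claiming efficacy in one sex.
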